### Brain MRI

2.2

Anatomical and DTI: In order to guide the TMS, all participants will undergo a brain MRI for brain lesions that are structural to generate a high-resolution anatomical brain image In addition, to examine structural brain integrity, T1 image volumes will be examined in 2 primary ways a) Reconstruction which is surface based and cortical thickness analysis b) An analysis that is volume based of the amygdala, hippocampal formation and different subcortical structures. Furthermore, a diffusion tensor imaging study (DTI) will be acquired using a diffusion-weighted (DW)-EPI sequence. Probtracx (FSL) will be used to delineate corticospinal tracts and corpus callosal connectivity.

### Assessments – instruments of evaluation

2.3

A rater blinded to the treatment will assess the effects of the interventions using the instruments described below. Subject enrollment, consent checklist, and screening logs will be used as well as an inclusion and exclusion checklist to assist in prescreening measures. To assess treatment efficacy (motor function changes), we will use the following instruments:

(1) *The Jebsen Taylor Hand Function Test (JTHF)* - this test was designed as a broad measure of hand function. This test has been used by our and other groups to assess the effects of tDCS on motor function in stroke the (2) *Purdue Pegboard Test* which is a test that is more sensitive to measuring changes in finger dexterity. To characterize motor function at baseline, we will use the following instruments: (3) *Fugl Meyer Assessment of Motor Recovery:* this tool is a progressive assessment which measures balance, motor recovery, sensation and a few joint functions in individuals with hemiparesis. Also, it includes elements which address speed and coordination (4) *Modified Barthel Index Score (Activities of Daily Living):* this tool assess the disability degree in each individual. It records the independence indicators in regards to the disability caused by impairments. The score ranges from 0 to 20 and it is mainly concerned with physical aspects of disability. Finally, we will use (5) *the Modified Ashworth Scale:* this instrument is a 6-point rating scale that is used to measure muscle tone. In addition, we will use the *visual analog scale* for anxiety and the visual analog scale for Pain / Comfort. Finally to measure the adverse effects of the interventions of this study, we will use (6) the *Mini Mental State Examination (MMSE):* is a short screening tool go assess cognitive abilities. We will use it as a quick screening method to assess any cognitive alterations that could have occurred from before or after treatment or even at follow up. The consistent scores of MMSE can suggest that the patient had no changes in cognition throughout the intervention period, which could have affected the test performance or the continuation of the program. (7) Adverse event monitoring and reporting: At each session, the patient will be asked using open-ended questions about adverse events and (8) *Transcranial Magnetic/ Direct Current Stimulation Adverse Effects Questionnaire*: at each session, a questionnaire will be filled by the subject to assess potential common adverse effects of TMS/tDCS (redness at the site of stimulation, itching, neck pain and headache,) on a 5-point scale.

These instruments will be performed at the following time points by trained staff blinded to group assignment: during the week before the beginning of treatment (2) During day 5 and day 10 of treatment and (3) at 2 weeks of follow up, 4 weeks and 6 months after the end of treatment (Table 1). Moreover, to make sure that blinding is not broken within the duration of the study, we will use a questionnaire to assess the validation of the blinding at the end of the study. This questionnaire will ask both the participants and the rater whether the treatment was sham or active tDCS. The confidence of the responses will be rated accordingly, from 0 to 5, where 5 is total confidence and 0 is no confidence,

**Table 1 T1:** Stroke and plasticity schedule of events.

	Screening visit	Training and tDCS Visits (10 d)			Follow-up visit
	1	2	6	10	4 wk
Consent	X				
Inclusion/Exclusion	X				
Pregnancy Test if indicated	X				
PMH/Physical	X				
Demographics	X				
Taylor Hand Function Test	X				X
Purdue Pegboard Test	X				X
Fugl-Meyer Assessment of Motor Recovery	X				X
Modified Barthel Index	X				X
Modified Ashworth Scale	X				X
Visual analog scale	X				X
Mini Mental State Examination		X	X	X	X
TMS and tDCS Screen	X	X	X	X	X
Training		X	X	X	X
MRI	X		X		
Pre/Post TMS Side Effect Questionnaire		X	X	X	X

MRI = magnetic resonance imaging, tDCS = transcranial direct current stimulation, TMS = transcranial magnetic stimulation.

### TMS methodology

2.4

Navigated Brain Stimulation (NBS) system (ANT, NLtm) will be used to deliver TMS by a figure-of-eight (F8) coil coupled with a Magpro stimulator (MagVenture, Denmark). Navigated TMS has the ability to online monitor the targeted cortical region, coil position, and orientation within and across sessions by using structural MRI. It delivers trial-by-trial information of an induced electric field for each TMS pulse and the localization of the induced current maxima. Data obtained by this system are reproducible, which is an essential aspect of this type of study. The display of induced currents and calculation will assist to overcome the constraints of TMS by targeting relevant structures of brain alone. As differences between different individuals in structure–function relationships, may change the induced currents and precision of the neuronavigation system, particularly in individuals with brain pathology.^[28]^

**The repetitive TMS paradigm** will be administered at 1 Hz frequency and consist of 2000 pulses delivered over a 30 minute period at 90% of the patient's motor threshold. These parameters are known to cause brain activity inhibition. The optimal stimulation site (First dorsal interosseus and APB muscles), active and resting threshold will be established in the unaffected and affected hemispheres. Assessment of EMG signals will be done at a rate of 5000 Hz. Cortical silent period (cSP) and resting and active motor threshold (RMT, AMT) will be analyzed according to the IFCN guidelines.

**Transcranial direct current stimulation (tDCS)** individuals participating were seated in a comfortable chair. The use of the StarStim NE noninvasive wireless tDCS/EEG neurotransmitter (NE Neuroelectrics, Barcelona, Spain) was used to deliver the direct current sequentially and record the EEG data. A placement of small Ag/AgCl gelled electrodes was done over the lesioned hemisphere (anodal) and area F3 (return electrode), with a surface contact area of 3.14 cm2 specific to the StarStimNE device (Pi electrodes, Neuroelectrics). A control box device, which is wirelessly connected to a computer and communicated with the NIC (version 1.2, Neuroelectrics), will be connected to the electrodes. throughout anodal stimulation, delivery of direct current took place from a current-control circuit at an intensity of 1.5 mA and maintained for 20 minutes. As for the sham stimulation, placement of the electrodes was done in the same position and individuals participating were given a short ramp up (20 s total up/down) at the start and end of the stimulation period.

**Assessment of cortical excitability** – single and paired pulse TMS We will investigate changes in cortical excitability evaluating the motor evoked potential and the resting motor threshold (we will use the same methods as in our previous study, using the technique of paired-pulse for intracortical excitability and transcallosal inhibition in order to measure interhemispheric differences.^[13]^ Both the affected and unaffected primary motor cortex will be studied. We will use the following inter-stimulus interval – 2, 4, 6, 10 and 12 ms. The percentage of inhibition or facilitation for each ISI before and after treatment will be calculated. To measure changes in transcallosal inhibition, a suprathreshold stimulus is applied to the motor cortex of 1 hemisphere, and ten milliseconds later a threshold stimulus is applied to the contralateral motor cortex. The percentages will be calculated for each stimulus for before and after treatment.

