### Genetic influence on inter-individual variability, plasticity and behavior

1.5

Genetic polymorphism is also a contributing factor to affect the brain's response to disease and injury. Brain-derived neurotrophic factor (BDNF) is involved in the modulation of synaptic plasticity which is activity-dependent in the human motor cortex. A common single nucleotide polymorphism (BDNF val66met) in BDNF gene, has been associated with a decrease in the secretion of BDNF which then decreases the activity-related cortical plasticity following healthy individuals’ motor training and is associated with more errors and deficient retention in short-term motor learning.^[21,22]^

We therefore hypothesize that neuronavigation 1 Hz rTMS on health side, which provides real-time feedback and allows stimulation only when trajectory, coil position and coil rotation are within consistent, pre-determined boundaries, will be a more potent effect on the excitability of specific local cortical networks (identified during the optimal site assessment), prime with tDCS on affected side will enhance the effects of CIMT on motor function recovery in chronic stroke patients. Until recently the use of noninvasive brain stimulation coupled with motor learning was limited as rTMS or tDCS alone.

Currently, detailed information about stroke or brain plasticity is not available in the Middle East.

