### Overall strategy

2.1

Overall Approach, Participants, and Feasibility: We propose to study 40 patients (above 18 years) with first-time clinical ischemic or hemorrhagic cerebrovascular accident. Individuals with preexisting neurological or psychiatric conditions, those with unstable medical conditions, and those on any medication that might alter the TMS-tDCS measures will be excluded. A written consent will be obtained, and all the subjects will have full neurological and medical examination. Furthermore, detailed neuropsychological and behavioral assessment will also be performed in different domains. All participants will undergo a neurophysiologic study of local cortical reactivity, plasticity, and network dynamics using TMS-EMG following stroke. Participants will be randomized to active treatment with 1 Hz rTMS prime with real anodal or sham tDCS by means of randomization stratification. This approach guarantee that both groups have a close distribution in regards to the degree of paresis. Participants will be gathered into groups (strata) defined by the degree of paresis (low and high functional) and then randomized separately within each stratum according to a block randomization of 4 to receive real 1 Hz rTMS prime tDCS/CIMT and sham tDCS/CIMT. All participants will undergo brain magnetic resonance imaging (MRIs) for morphometric analysis and diffusion tensor imaging, and serial neurological and neuropsychological exams.

We have developed a safe and reliable method combining TMS with EMG to characterize cortical reactivity, plasticity, and brain network dynamics in humans.^[23–27]^

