### Constraint induced movement therapy (CIMT)

2.5

Each subject will receive 14 days (2-week period: 10 weekdays) of CIMT (using the same methodology as described in a recent multi-site clinical trial.^[15]^ furthermore, during the 10 weekdays of the treatment period, the individuals participating will come into the laboratory to train the affected arm for up to 6 hours a day, using a variety of tasks according to a behavioral technique termed “shaping.”

**Statistical power and data analysis Sample size** will be determined with reference to other studies that used similar endpoints. We assume that a standardized difference of 0.8 (the difference between groups divided by the standard deviation) is conservative to detect a clinically meaningful difference between groups (active 1 Hz rTMS prime with tDCS/CIMT and sham tDCS/CIMT). We will assume a type I error of 5% (alpha), a type 2 error of 10% (beta), therefore, the power is going to be 90%. A t-test will be used (Using the sample size calculation for a normal distributed population); where 15 individuals per arm will be needed (therefore, a total of 30). We expect a 20% rate of loss to follow up or drop out. Moreover, we will assume that individuals who drop out will not improve from the last measured point; therefore, the sample size will increase by 20% to 36 participants (18 per arm). Furthermore, in case of unexpected factors such as higher placebo response, we increased the sample size further to 40 patients.

**PROTECTION OF HUMAN SUBJECTS** This study aims to enroll adult patients with a history of cerebral infarct that is chronic and associated with stable and significant motor deficits. Both ischemic and hemorrhagic stroke subtypes will be included. The entry criteria for patient enrollment are the following:

(1)age 18 to 90;(2)first-time clinical ischemic or hemorrhagic cerebrovascular accident as noted in the radiological (or physician's) report;(3)the ability to extend =20° at the wrist and 10° at the metacarpophalangeal and interphalangeal joints of all digits;(4)participants must demonstrate adequate balance while wearing the restraint;(5)the ability to stand from a sitting position and the ability to stand for at least 2 minutes with or without upper extremity support;(6)weakness, defined as score of 15 to 55 (out of 66) on arm motor Fugl-Meyer scale; and(7)stroke onset more then 6 months prior to study enrollment.

*Exclusion criteria*:

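### The stated rTMS dose contradicts itself: 1 Hz for 30 minutes gives 1800 pulses, not 2000

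*Protocol article*

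**What the plan says.** Section 2.4 (TMS methodology) of the protocol article describes the repetitive TMS as "1 Hz frequency and consist of 2000 pulses delivered over a 30 minute period", at 90% of motor threshold. The next sentence rests the rationale on that set of values: "These parameters are known to cause brain activity inhibition".

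The frequency appears in three other places:

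- Section 1.5, in the hypothesis: "neuronavigation 1 Hz rTMS on health side".
- Section 2.1 (Overall strategy), in the randomisation description: "active treatment with 1 Hz rTMS prime with real anodal or sham tDCS".
- Section 2.5, in the sample-size paragraph, which names the comparison: "active 1 Hz rTMS prime with tDCS/CIMT and sham tDCS/CIMT".

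The pulse count and the length of rTMS stimulation appear only in section 2.4.

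**The concern.** Frequency, pulse count and duration are tied together: any two determine the third. Section 2.4 gives all three, and they disagree. Nothing there describes trains, a second block or an approximate value that would reconcile them.

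What is at stake is whether the intervention can be delivered and replicated as written. rTMS is one of the stimulation components under test, and this sentence is the only place its dose is given. An operator who stops at 30 minutes gives 1800 pulses. One who stops at the pulse count gives 2000 and runs past 33 minutes. Both could claim to have followed the protocol. Section 2.4 itself stresses reproducibility as a reason for using navigated stimulation, and it gives the tDCS dose (1.5 mA for 20 minutes) without any such conflict.

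**Working it through.** **Inputs, from the rTMS sentence in section 2.4**

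- Frequency f = 1 Hz, that is, one pulse per second (also in sections 1.5, 2.1 and 2.5)
- Pulse count N = 2000
- Duration T = 30 min = 30 × 60 = 1800 s

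**Reproducing the stated pulse count**

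N = f × T = 1 × 1800 = 1800 pulses. The stated 2000 is not reproduced. The difference is 2000 − 1800 = 200 pulses, which is 200/2000 = 10% of the stated count, or 200/1800 = 11.1% above the computed one.

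**Solving for each figure in turn**

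| Held fixed | Solved for | Result | Stated |
|---|---|---|---|
| 1 Hz, 30 min | pulses | 1 × 1800 = 1800 | 2000 |
| 1 Hz, 2000 pulses | duration | 2000/1 = 2000 s = 33 min 20 s | 30 min |
| 2000 pulses, 30 min | frequency | 2000/1800 = 1.11 Hz | 1 Hz |

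In time, the gap is 2000 − 1800 = 200 s = 3 min 20 s, which is 200/1800 = 11.1% of the stated duration.

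**Could an unstated train structure explain it?** No. Pauses between trains within the 30 minutes would reduce stimulation time and bring the count below 1800, which widens the gap.

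**Which figure is the anchor?** A rate of 1.11 Hz would reconcile the other two, but 1 Hz is the name the article gives the intervention throughout. The error therefore lies in the pulse count or the duration. Each is stated only once, so the document cannot settle which.

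**The case against.** The arithmetic is not open to dispute. The case on the other side is that the matter is small, and it has several parts.

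- **Rounding.** The pulse count is what is programmed into a stimulator, and 30 minutes may be a loose figure for 33 min 20 s. This is the most natural charitable reading and may be what was meant. The text gives no sign of it, however, and a reader cannot rule out 1800 pulses.
- **Inhibitory effect.** Both possible corrections keep 1 Hz and 90% of motor threshold, and nothing in the article suggests that 1800 rather than 2000 pulses changes the direction of the effect. This stands. The claim of inhibition is not shown to fail at either dose; the point is only that it refers to a set of values that cannot be delivered exactly.
- **Treatment contrast.** Section 2.1 can be read as giving both arms the same rTMS, with only the tDCS real or sham. On that reading the uncertainty is common to both arms and would not by itself bias the comparison. Other passages can be read differently, so this is unsettled. It limits the consequence but does not make the dose definite.
- **Per session.** The rTMS sentence does not say that its figures apply to each session, and the number of rTMS sessions is not stated. Treating the gap as a per-session figure is an inference, though a reasonable one.
- **Condensed article.** Operating detail, such as what ends a session, is often left to the full protocol. That is fair as to what is missing, but it does not excuse a stated dose that contradicts itself.

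These points bear on the weight of the finding, not on whether it is true.

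**Conclusion.** The concern holds. The three rTMS parameters in section 2.4 cannot all be correct. With 1 Hz kept, the stated dose is off by 200 pulses (10% of 2000) or by 3 min 20 s (11.1% of 30 minutes) per application.

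This rests on two assumptions: that 1 Hz is the intended frequency, which its repetition elsewhere supports, and that the sentence describes one session. Whether the count or the duration is at fault cannot be determined from the article.

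The consequence is confined to how the intervention is specified, delivered and replicated. Sample size, power and endpoints are untouched, and the article gives no basis for claiming an effect on safety or efficacy. It should be corrected because it is the sole dose statement for a core component, but it does not threaten the design.

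**What to change.** Keep 1 Hz and rewrite the sentence in section 2.4 in one of two ways:

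- 1 Hz, 1800 pulses over 30 minutes; or
- 1 Hz, 2000 pulses over about 33 minutes (33 min 20 s).

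The sponsor must choose, since only the sponsor knows which was intended. The sentence should add that the pulse count ends the session, so that all operators stop at the same dose. If participants have already been treated, report the dose actually delivered.

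The cost is one sentence. No design element, sample-size figure or analysis changes.

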**Methods::**

Herein, we propose to enhance the effects of brain plasticity using a powerful noninvasive technique for brain modulation consisting of navigated transcranial magnetic stimulation (TMS) priming with transcranial direct current stimulation (tDCS) in combination with motor-training-like constraint-induced movement therapy (CIMT). Our hypothesis is that navigated low-frequency rTMS stimulus priming with precise location provided by neuronavigation on the healthy side of the brain and with anodal tDCS on the affected side combined with CIMT will induce a greater motor function improvement than that obtained with sham tDCS combined with CIMT alone. We predict that the application of this technique will result in a large reduction in cortical excitability and dis-inhibition in the affected hemisphere and lead to improvements in behavioral measures of hand function in stroke patients.

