### Understanding stroke recovery mechanism based on brain plasticity is critical for developing new therapeutic approach

1.2

Brain plasticity is the ability of the brain to adapt to experiences, environmental pressure, and challenges which include brain damage.^[5,6]^ It happens within many levels, from molecules to cortical reorganization. There are multiple factors that influence the outcome of stroke, including the time after stroke, the lesion's location and the integrity of cortico-spinal tracts, and the cortical and subcortical connections. In general, each hemisphere undergoes neuroplasticity changes by means of regeneration, for example, axonal and dendritic sprouting with or without reorganization of cortical motor areas, for example, modulation of the synaptic plasticity or remapping of the functional representations by diminution of GABAergic inhibition, and increased NMDA receptor binding from lessoned areas onto the unaffected ipsilesional areas which surround the lesion or the homologous areas which are within the contralesional unaffected hemisphere.^[7,8]^

The latest literature specifies that noninvasive brain stimulation (NIBS) techniques (i.e. repetitive transcranial magnetic stimulation (rTMS) and transcranial direct current stimulation (tDCS)) can enhance the recovery of motor functions in chronic stroke patients. Two potential roles have been described for rTMS and transcranial direct current stimulation (tDCS) in stroke recovery:

(1)to inhibit, that is, downregulate, the healthy hemisphere, or(2)to enhance excitability of the lesioned hemisphere.

Downregulation of the contralesional hemisphere can lead to improved motor performance in the affected limb, thought to be through a reduction in interhemispheric inhibition to the lesioned side. Most of the spontaneous stroke recovery after the acute phase entails plastic changes within the brain.^[9]^ For rehabilitation, new measures should be adopted to facilitate plasticity of brain which help in changes to occur more rapidly and more completely. Since plasticity in the hemisphere with stroke lesions leads to good recovery, one therapeutic approach such as brain stimulation should be focused to enhance brain plasticity in these areas.

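### Transcallosal inhibition is tested with a pulse at motor threshold, which distorts the inhibition percentage in a direction that depends on an unstated scoring rule and on EMG noise

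*Protocol article*

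**What the plan says.** Section 2.4 (TMS methodology, assessment of cortical excitability) gives both pulses in one sentence. The conditioning pulse, on one side, is above threshold. The test pulse on the other side is not: "ten milliseconds later a threshold stimulus is applied to the contralateral motor cortex". The outcome is a percentage: "The percentages will be calculated for each stimulus for before and after treatment".

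The same section says of both cortices: "Both the affected and unaffected primary motor cortex will be studied". Thresholds are defined by reference only: "resting and active motor threshold (RMT, AMT) will be analyzed according to the IFCN guidelines". The article does not say whether the test pulse is at resting or active threshold, or how a trial without a response is scored. For the paired-pulse method it points to earlier work: "we will use the same methods as in our previous study".

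Section 1.2 explains why the measure is there. The benefit of downregulating the healthy hemisphere is "thought to be through a reduction in interhemispheric inhibition to the lesioned side". The abstract predicts that the treatment "will result in a large reduction in cortical excitability and dis-inhibition in the affected hemisphere".

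**The concern.** Inhibition is read as a reduction of the test response, so that response needs room to fall. A pulse at motor threshold, in the usual sense of a just-detectable response in about half of trials, leaves little room. The conditioned response then drops mostly below what can be detected. What the percentage shows is governed by the noise floor, or by the convention for absent responses, as well as by the inhibition itself.

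The transcallosal test is the only direct physiological measure of inhibition between the hemispheres that the article describes, and section 1.2 makes that inhibition the route by which healthy-side stimulation should help. At stake is whether the trial can say how far that mechanism changed. The efficacy comparison on hand function is not at stake.

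**Working it through.** The article gives no amplitude, variance, number of trials or expected change for this measure, so there is no figure to reproduce. The check below is illustrative.

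**From the article:** suprathreshold conditioning pulse; test pulse at threshold, 10 ms later; outcome is a percentage before and after treatment.

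**Assumed:**
- median unconditioned response M = 50 microvolts at threshold, or 1000 microvolts for a clearly suprathreshold test pulse
- log-normal trial-to-trial variation with log-SD s = 0.6, 0.8 or 1.0
- noise floor f = 10, 20, 30 or 40 microvolts
- detection criterion 50 microvolts
- true inhibition 75% before and 50% after treatment (change of 25 points)

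The conditioned median is m = M × (1 − inhibition): 12.5 microvolts at 75% and 25 at 50%. Recorded inhibition = 100 × (1 − mean conditioned / mean unconditioned).

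**Step 1: how many trials give a response?** By construction half of the unconditioned trials fall below 50 microvolts (33% to 49% in a variant with noise of 10 to 30 microvolts added in quadrature and log-SD 0.5 or 0.8). The share of conditioned trials that reach 50 microvolts is 1 − Φ(ln(50/m)/s): 1% to 8% at 75% inhibition and 12% to 24% at 50%.

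**Step 2: small responses read at the noise floor.** Each trial is recorded as the larger of response and f, so the mean is f·Φ(ln(f/m)/s) + m·exp(s²/2)·Φ((ln(m/f)+s²)/s). For s = 0.8 and f = 30 the means are 71.53 (unconditioned), 32.51 (at 75%) and 42.37 (at 50%). Recorded inhibition is 1 − 32.51/71.53 = 54.5% and 1 − 42.37/71.53 = 40.8%, a change of about 13.8 points.

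Recorded change, true change 25 points:

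| log-SD | f = 10 | f = 20 | f = 30 | f = 40 |
|---|---|---|---|---|
| 0.6 | 23.4 | 16.7 | 10.2 | 6.0 |
| 0.8 | 23.4 | 18.6 | 13.8 | 10.0 |
| 1.0 | 23.5 | 20.1 | 16.5 | 13.5 |

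The loss is slight at 10 microvolts and large at 40.

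**Step 3: responses below the criterion scored as zero.** The mean is m·exp(s²/2)·Φ((ln(m/50)+s²)/s). For s = 0.8, a true 75% is recorded as 1 − 0.25 × Φ(−0.933)/Φ(0.8) = 1 − 0.25 × 0.1754/0.7881 = 94.4%.

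| log-SD | true 75% reads | true 50% reads | change |
|---|---|---|---|
| 0.6 | 98.5% | 80.1% | 18.4 |
| 0.8 | 94.4% | 70.0% | 24.5 |
| 1.0 | 89.6% | 63.1% | 26.5 |

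The level is overstated throughout, while the change may be nearly right. With other values (true 60% to 30%, quadrature noise of 10 to 30 microvolts, log-SD 0.5 or 0.8, 15 trials) the true 30-point change is recorded as 19.0 to 27.6 points from raw amplitudes and 38.6 to 42.6 points with zero scoring. So the direction of the error in the change is not fixed.

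**Step 4: precision.** In that second set, the between-run SD at 30% inhibition is 23 to 43 points with zero scoring, against 14 to 26 points with a large test response. Raw-amplitude scoring is not noisier (11 to 25 points). At strong inhibition, zero scoring can look stable only because values pile up at 100%: with 15 trials and true 75%, the chance that no conditioned trial reaches the criterion is (1 − 0.0416)^15 = 53% at log-SD 0.8 and (1 − 0.0104)^15 = 85% at log-SD 0.6.

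**Step 5: the same model with a large test response.** With M = 1000 microvolts, 75% and 50% are recorded to within about 0.1 point in every cell, under both scoring rules.

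**The case against.** The strongest reply has four parts.

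- *The definition of threshold is not in the article.* True: the 50%-of-trials and 50-microvolt conventions are assumptions here, and the resting or active threshold is left open. The sentence still contrasts a suprathreshold pulse with one at threshold, so the low intensity is a stated choice.
- *The method is deferred to an earlier study and the article is condensed.* Scoring rules and amplitude targets may well stand elsewhere, and their absence is not the complaint. The printed test intensity is. If the team already uses a stronger test pulse, the sentence needs correcting.
- *The size depends on the noise floor.* This stands. Nothing in the article fixes it, and at 10 microvolts more than 23 of the 25 points are kept.
- *The measure is secondary to the trial's purpose.* This also stands. Efficacy is judged on hand-function tests, the sample size is not stated to rest on this measure, and excitability within each hemisphere is assessed in other ways.

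A reader might infer that the endpoint sits on its floor, that its change must be compressed, or that strong and reduced inhibition would look alike, so that a real mechanism would be declared absent. The material does not support this. About half or more of the unconditioned trials still give a detectable response, and it is the conditioned response that nears the floor. Compression holds with noise-floor scoring but not in general with zero scoring. The two states remain 6 to 24 points apart on average even with noise-floor scoring.

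**Conclusion.** The point holds as a measurement weakness. As written, the test pulse gives a poor base for an inhibition ratio, and the recorded percentage depends on noise and on a scoring convention as well as on inhibition. Under the stated assumptions a true 25-point fall is recorded as about 6 to 24 points with noise-floor scoring at 10 to 40 microvolts. With zero scoring it is recorded as 18 to 27 points, with the level overstated (true 75% read as about 90 to 98%) and a wider spread at moderate inhibition. All amplitudes, variances and noise levels are assumptions, as is the usual meaning of motor threshold.

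The consequence is limited to the mechanistic claim about inhibition between the hemispheres. The change is worth making because it is cheap and removes the dependence on scoring; the motor-function conclusion does not turn on it.

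**What to change.** In section 2.4, replace the threshold-level test pulse for transcallosal inhibition by a suprathreshold test pulse, set individually to give a stable, clearly measurable unconditioned motor evoked potential. Re-set it to the same target amplitude at each assessment, since treatment is expected to change excitability. Compute inhibition from the ratio of conditioned to unconditioned amplitude (100 × (1 − ratio)). Where no such response can be obtained, record the measure as not obtainable rather than as 100% inhibition.

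The change concerns an assessment pulse, not the treatment. It costs one phrase in the procedure and a few more minutes of set-up, with the same equipment and visits. The small downside is that some patients, for instance those with a high threshold on the affected side, will have no value.
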